#### Stool

Infant feces are used for microbiome profiling. Once the infant has a bowel movement, the stool is scored by the mother for consistency, color, and volume. About 1 g of the specimen is collected with the spoon (attached to the cap) of the feces collection tube. The spoon is placed into the collection tube and stored at –80°C. If the specimen is collected outside the clinic (not applicable in The Gambia, all stool sample collection here is conducted at the study site), it must be stored in the home freezer and delivered frozen, on ice, for –80°C storage as soon as possible. All participants have been instructed by the field study staff and have confirmed the availability of a freezer for eligibility of at-home stool collection. All times of collection and storage are recorded.

### Laboratory analyses

All samples except those to be used for iodine and milk volume determination are shipped to the USDA, Agricultural Research Service-Western Human Nutrition Research Center (USDA, ARS-WHNRC), Davis, CA, USA. At each site, the research personnel prepare the aliquots for the following analyses (Table 3). Samples for human milk vitamin D analysis will be sent from the USDA/ARS-WHNRC to the Nutritional Biomarker Laboratory, MRC Epidemiology Unit, University of Cambridge, Cambridge, UK.

#### Data management

A dedicated, REDCap database was developed at a single site (The Gambia) to be used across all study settings. Unique α-numeric study ID codes are generated and given to each participant. These will link all data collected from a specific individual. ID codes include a check letter to minimize ID errors. Data collection is carried out electronically, or on paper forms when necessary, by study staff. All forms in the field were designed specifically for the MILQ Study. Research assistants and supervisors review data on a daily basis before data from each field site is securely integrated into The Gambia REDCap database by a data manager. A copy of the final data obtained from the laboratory/analytical sites is reviewed by the study statistician before being securely integrated in a WHNRC-housed REDCap database. Both databases will be merged at the end of the field site data collection and integration. Data management and security procedures, including assurance of confidentiality, adhere to the Collaborative Institutional Training Initiative (CITI) and the Canadian Tri-Council Policy Statement on Ethical Conduct for Research Involving Humans (TCPS2 CORE) guidelines, and are outlined in full in the protocol at clinicaltrials.gov (NCT03254329, 18 August, 2017).

### Statistical analysis

#### Sample size calculations

Since the primary outcome is estimated key centiles of the distributions of nutrient concentrations in human milk, and centiles are invariant to monotonic transformation, sample sizes for constructing RVs are based on: *1*) estimating the 50th and 5th percentiles of each breast milk nutrient across time periods within each site and *2*) being able to establish equivalency among study sites before pooling data.

#### Estimating centiles

We aim for a monotonic transformation for each variable across all study sites to attain normal (Gaussian) distribution, from which parametric estimates of the centiles will be constructed. Regression models will be used to estimate the parameters of the distribution at each time period, but since such models will not be determined until the data are available, the sample size is based on a generic estimate for the p^th^ centile:
(1)}{}\begin{eqnarray*} \bar{X} + {Z_p} \times s \times C{F_s} \end{eqnarray*}where:

}{}$\bar{X}$
 = sample mean (or estimated predicted value from the regression model)

*Z_p_* = p^th^ centile of the standard normal distribution (negative for *P* <0.50)

}{}$s$
 = sample SD (or estimated SD from regression model)

*CF_s_* = correction factor for bias of s as an estimator of population SD (negligible for *n* >50).

The SE of this estimate, if *n* is >50, is approximately:
(2)}{}\begin{eqnarray*} \frac{\sigma }{{\sqrt n }}\sqrt {1 + 0.5 \times Z_\alpha ^2} \end{eqnarray*}

The desired width of the CI is based on the distance of the 50th and 5th centiles from neighboring centiles, which yields a sample size invariant to the location, scale, or shape of the underlying distribution, as long as the variable can be normalized. This requires an overall sample size of 255 per time point to avoid overlap between the 95% CIs around the 5th and 10th centiles, and to estimate the sample median within 5 centiles with 95% confidence (**Table 4**). Once the centiles of interest are estimated for the transformed variable, they will be back-transformed to be expressed in the original units.

**TABLE 4 tbl4:** Planned analyses in the Mothers, Infant, and Lactation Quality (MILQ) Study

Analyte Category	Analytes	Milk	Blood	Urine	Stool	Method	Ref.^1^
Fat-soluble	Vitamin A	X	X^P^			HPLC-MWL	(31)
vitamins and carotenoids	Vitamin E						
	α-carotene						
	β-carotene						
	β-cryptoxanthin						
	Lycopene						
	Lutein/zeaxanthin						
	Ergocalciferol (D_2_)	X	X^P^			UPLC-MS/MS	
	Cholecalciferol (D_3_)					CPBA	(32)
	25-OH-D_2_						
	25-OH-D_3_						
Water-soluble vitamins	Thiamin (B-1)	X	X^R^			HPLC-FLD	(33)
	Thiamin monophosphate (B-1)						
	Thiamin diphosphate (B-1)						
	Riboflavin (B-2)	X	X^P,R^			UPLC-MS/MS	(27)
	FAD (B-2)						
	FMN (B2)						
	Nicotinamide (B3)						
	Nicotinic acid (B-3)						
	Nicotinamide mononucleotide (B-3)						
	NAD (B-3)						
	NAD(P) (B-3)						
	Nicotinamide riboside (B-3)						
	Tryptophan (amino acid, B-3-related)						
	Pantothenic acid (B-5)						
	Pyridoxal (B-6)						
	Pyridoxine (B-6)						
	Pyridoxamine (B-6)						
	Pyridoxal 5-phosphate (B-6)						
	Biotin (B-7)						
	Folic acid (B-9)						
	5-methyl tetrahydrofolate (B-9)					CPBA^2^	(34)
	Cobalamin (B-12)	X	X^P^			CPBA	(28, 35)
Choline and related	Choline	X	X^P^			UPLC-MS/MS	(36)
metabolites	Phosphocholine						
	Glycerophospho choline						
	Betaine						
	Carnitine						
	Creatinine						
	Dimethylglycine						
	Methionine						
	Trimethylamine N-oxide						
B-12 biomarkers	Methylmalonic acid		X^P^			UPLC-MS/MS	(37)
	Homocysteine		X^P^			HPLC-FLD	(38)
Minerals and	Iron	X	X^P^			ICP-MS	(39)
trace elements	Copper						
	Zinc						
	Selenium						
	Sodium						
	Potassium						
	Magnesium						
	Calcium						
Iodine status	Iodine	X		X		ICP-MS	(40)
	Thyroglobulin		X^DBS^			ELISA	(41)
	Thyroid-stimulated hormone						
	Total thyroxine						
Macronutrients	Protein	X				NIR-spectroscopy	(42)
	Fat						
	Carbohydrates						
Glycomics	Human milk oligosaccharides^3^	X				HPLC Chip/TOF-MS	(43)
	Human milk proteomics^4^	X				UPLC-QqQ-MS	(44)
Metabolomics	Biocrates MxP® QUANT 500^3^	X	X^P^			UPLC-MS/MS	(45)
Inflammation markers	α-1-acid glycoprotein (AGP)		X^P^			CPBA	(46)
	C-reactive protein (CRP)						(47)
	IL-1β, IL-4, IL-8, IL-6, IL-10, IL-33, TNF-α, IFN-γ	X	X			MSD immunoassay plates	(48)
Iron status	Soluble transferrin receptors		X^P^			CPBA	(49)
	Ferritin						(50)
Hormones	Leptin, insulin, and adiponectin	X	X			MSD immunoassay plates	(48)
Genetics	Single nucleotide polymorphism		X^B^			GWAS	(51)
	CpG methylation patterns		X^B^			EWAS	(52)
Microbiome	Microbial community				X	16s RNA sequencing	(53)
					X	Shotgun metagenomics	(54)
Transcriptomics	mRNA transcriptome	X^RNA^				RNA seq	(55, 56)

Analyzed in: ^B^buffy coat, ^DBS^dried blood spots, ^P^plasma, ^R^RBCs, ^RNA^RNA.

1 References that describe methods used for the analysis or on which the nonpublished methods are based on: CPBA, competitive protein binding assay; EWAS, epigenome-wide association; FLD, fluorescence detection; GWAS, genome-wide associations; ICP, inductively coupled plasma MS/MS; MSD, Meso Scale Discovery; MWL, multi-wavelength detection; NIR, near infra red; QqQ-MS, triple quad MS; TOF, time of flight; UPLC, ultra-performance-LC.

2 Plasma folate is analyzed by CPBA.

3
https://[name].faculty.ucdavis.edu/research/nutritional-glycomics/.

4
https://biocrates.com/mxp-quant-500-kit/.

For maternal and infant blood variables, it is likely that blood samples will not be available from all participants, so the sample size will be reduced by necessity. However, if it is determined that it's acceptable to pool information from ≥2 study sites to construct RVs for infant blood variables, the precision of the estimate will be acceptable.

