## Abstract

Little valid information is available on human milk nutrient concentrations, especially for micronutrients (MNs), and there are no valid reference values (RVs) across lactation. In this multi-center collaborative study, RVs will be established for human milk nutrients across the first 8.5 mo postpartum. Well-nourished, unsupplemented women in Bangladesh, Brazil, Denmark, and The Gambia (*n* = 250/site) were recruited during the third trimester of pregnancy. Milk, blood, saliva, urine, and stool samples from mothers and their infants are collected identically at 3 visits (1–3.49, 3.5–5.99, 6.0–8.49 mo postpartum). Milk analyses include macronutrients, selected vitamins, trace elements and minerals, iodine, metabolomics, amino acids, human milk oligosaccharides, and bioactive peptides. We measure milk volume; maternal and infant diets, anthropometry, and morbidity; infant development, maternal genome, and the infant and maternal microbiome. RVs will be constructed based on methods for the WHO Child Growth Standards and the Intergrowth-21st Project. This trial was registered at clinical trials.gov as NCT03254329.

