#### Establishing equivalency among study sites

For each nutrient and time period, pairwise comparisons using the 2, 1-sided test (TOST) method will be used to compare the means of the 4 sites for equivalence (20). If differences >0.3 SD are detected, a follow-up test will be conducted to compare each mean to the combined means of the other 3 sites, to determine which sites can be pooled. A sample size of 200 per site in each time period is sufficient to detect differences of 0.25 SD with 80% power or differences of 0.30 SD with 90% power. Therefore, the planned sample size of 250 per site and time period will provide adequate power to determine whether 1 site is different from the others (**Table 5**).

**TABLE 5 tbl5:** Required sample sizes for testing equivalence

Differences (site means)	Sample size/site 80% power	Sample size/site 80% power
0.20 SD	310	429
0.25 SD	199	275
0.30 SD	139	191

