#### Sample size estimates for other analyses

For some secondary outcome variables, e.g. free amino acids (FAA) in infant plasma, a complete sample set for analyses is not feasible or available. In such cases, only 100 samples for each site and time point are analyzed, assuming a priori that the values are similar enough to pool between ≥2 of the sites. If this is not possible, within-site percentiles will be presented with a caveat that these should not be considered as RVs, as precision is limited. However, 100 per time point is ample for looking at relations between secondary outcome variables and other outcomes, such as growth. Nevertheless, banked samples are available if initial data analyses show that analysis of >100 samples per point is needed.

Future exploratory analyses will also assess the relations between milk nutrient concentrations and other collected information, including milk volume, child growth, child developmental milestones, and maternal and infant plasma values. A sample size of 140 paired data points per site and time period is adequate to detect a correlation between continuous variables of 0.30 or higher with 95% power within each site, assuming a 2-sided alternative hypothesis, and therefore the planned sample size of 250 per site and time point is more than sufficient for these analyses.

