## Discussion

Although the importance of human milk in maternal and infant nutrition has long been recognized, the MN intake recommendations for breastfeeding infants and lactating women are still based on old, uncertain, or even incorrect data (4) and are established mainly as Adequate Intakes for infants due to the lack of experimentally determined estimates of milk composition and nutrient requirements (23). Further, the dynamic changes in concentrations of many milk nutrients across lactation are not reflected in the current recommendations, which can lead to erroneous status evaluations (24, 25). Therefore, given the importance of adequate nutrient intake during the first 1000 d of life (26), which includes the WHO-recommended 6-mo period of EBF (1), this systematic, longitudinal assessment of the nutrient composition of human milk, in particular for MNs, using validated methodologies, is indispensable for correctly evaluating nutrient intake adequacy of breastfeeding infants.

We have developed and validated multiple novel methods for collecting and analyzing human milk (24, 27–30), which will be used or further optimized for the nutrient assessment in this study. The identical collection protocols and methods for analyzing human milk and blood samples minimize method bias and enable direct comparison between field sites. The inclusion and exclusion criteria, and collection of information on diets, anthropometry, and infant developmental milestones provide supportive information that participants are healthy and nutrient sufficient.

The 4 field sites are different in demographics, socioeconomic status, diets, and cultural practices which may preclude combining data across sites to establish the RVs, but the required number of participants per site allows for the creation of study-site-specific RVs if necessary.

The longitudinal data obtained by the staggered sample collection protocol will allow for the development of new dynamic RVs, providing percentile ranges for every stage of lactation covered in this study. These carefully developed RVs, in conjunction with the milk volume data, will be available for re-evaluating intake recommendations for infants, young children, and lactating women, and as benchmarks against which to evaluate human milk quality, and the effects of future nutrient intervention trials on milk composition.

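### The per-site sample of 250 meets the article's own centile-precision target only if no more than 6 dyads (2.4%) are lost at a site and visit, so the unqualified assurance on site-specific reference values needs qualifying

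*Protocol article*

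**What the plan says.** In the Protocol article, Sample size calculations gives as its first basis "estimating the 50th and 5th percentiles of each breast milk nutrient across time periods within each site". Estimating centiles then states the number: "This requires an overall sample size of 255 per time point to avoid overlap between the 95% CIs around the 5th and 10th centiles", together with a second criterion, "to estimate the sample median within 5 centiles with 95% confidence".

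The planned number is 250 per site. The Abstract gives n = 250/site for women who "were recruited during the third trimester of pregnancy". Establishing equivalency among study sites uses "the planned sample size of 250 per site and time period", and Sample size estimates for other analyses likewise uses 250 at each time point.

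Table 3 lists exclusions at visit 2 (stopped or non-exclusive breastfeeding, serious maternal illness, low infant Z scores, supplement use) and at visits 3 and 4 (stopped breastfeeding, low Z scores, abnormal development). The Data analysis plan also removes children who fail criteria for growth, development or nutritional status, and removes extreme outliers where needed. It names per-site centiles as one option if sites cannot be combined. The Discussion accepts that site differences may prevent pooling and adds that "the required number of participants per site allows for the creation of study-site-specific RVs if necessary".

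**The concern.** The precision goal is set within site and the stated requirement is slightly above the planned number. That planned number is used as if every recruited dyad supplied usable data at each visit, although the article itself provides for dyads to leave the reference sample. No loss allowance appears beside the centile calculation.

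This matters in the case the article foresees: sites that differ too much to be pooled. Single-site centiles then become the reference values, and a reader would take the Discussion to mean that they carry the precision set out under Estimating centiles.

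**Working it through.** **Inputs**
- Standard error of a centile, equation (2): σ/√n × √(1 + 0.5z²). The SD cancels.
- Criteria: 95% intervals for the 5th and 10th centiles do not overlap; median within 5 centiles with 95% confidence.
- Normal quantiles: z(0.05) = −1.645, z(0.10) = −1.282, z(0.55) = 0.1257.
- Factors √(1 + 0.5z²): 1.534 at the 5th centile, 1.350 at the 10th; sum 2.884. Distance between the two centiles: 0.3633 SD.
- Loss rates: none stated. The 10% and 20% below are assumptions.

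**Reproducing 255**

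Non-overlap: n = (m × 2.884 / 0.3633)². Median: n = (m / 0.1257)².

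| Multiplier m | Non-overlap | Median |
|---|---|---|
| 2 | 252 | 254 |
| 1.96 | 242 | 244 |

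The stated 255 is approached with the rounded multiplier 2. With 1.96 the binding minimum is 244. The text points to Table 4 for this figure, but Table 4 lists the planned analyses, so the authors' own steps cannot be seen.

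**Margin at the planned number**

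250 − 244 = 6 dyads; 6/250 = 2.4%.

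**Precision at the evaluable number (m = 1.96)**

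Gap between intervals = 0.3633 − 1.96 × 2.884/√n. Median error = Φ(1.96/√n) − 0.5.

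| Evaluable n | Gap between 5th and 10th intervals (SD) | Median within (centiles) |
|---|---|---|
| 250 (no loss) | +0.006 | 4.9 |
| 225 (10% loss) | −0.013 (overlap) | 5.2 |
| 200 (20% loss) | −0.036 (overlap) | 5.5 |
| 500 (two full sites) | +0.111 | 3.5 |

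On the centile scale, at 250 the 5th-centile interval ends at 7.29 and the 10th-centile interval begins at 7.37. At 200 they end and begin at 7.60 and 7.10. Two sites at 200 each still give 400, well above 255.

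**Recruitment per site that would preserve the target, n/(1 − loss)**
- To keep 244: 272 at 10% loss, 305 at 20%.
- To keep 255: 284 at 10% loss, 319 at 20%.

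**The case against.** Several points on the other side are sound.

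- **255 against 250.** A reader might infer that the plan misses its own requirement outright. It does not: with 1.96, a full 250 meets both criteria, and 255 is a slightly conservative figure.
- **What 250 counts.** Study design and settings describes samples taken from 250 dyads per country across the visits, Human milk and RNA speaks of 250 women at visit 2 in two countries, and Table 3 places enrollment after delivery in at least Bangladesh. The Abstract's recruitment count is therefore not the only reading. The article is unclear here, rather than shown to be counting before exclusions. Even so, the removals in the Data analysis plan come after collection.
- **Loss rate.** None is given, and the full protocol may hold an allowance. Table 1's exclusive breastfeeding rates of 50 to 71% at 2 months and 18.6% stunting in Bangladesh describe the settings, not these selected dyads. They do not establish any particular loss.
- **The word overall.** It could point to the pooled sample, but the preceding section sets the goal within each site, and 1,000 dyads would far exceed 255.
- **Generic formula.** Regression and spline smoothing will be used, so achieved precision may differ from this single-window calculation. The Discussion also says only that site-specific values can be created, without naming a precision.

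A reader might also take the analytes for which "only 100 samples for each site and time point are analyzed, assuming a priori that the values are similar enough to pool" as proof that site-specific values fail. They are not: these are secondary variables, the article already withholds reference-value status from their within-site percentiles, and it names banked samples as a remedy.

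**Conclusion.** The concern holds in a limited form. The article states a within-site precision and a per-site number that match only if at most 6 of 250 dyads (2.4%) are lost at a given site and visit. Given its own exclusions and removals, the unqualified Discussion sentence is not supported at that precision.

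The shortfall is modest. At 20% loss the median is known to within 5.5 rather than 5 centiles and the two lower-centile intervals overlap slightly. It would be wrong to infer that single-site values are unusable; they would be less precise than the stated target. Pooled values from two or more sites of about 250 are not affected.

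This rests on the within-site reading of the target, equation (2) with 1.96, variables that can be normalized, and loss rates assumed here.

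A separate, minor point concerns the 100-sample secondary analytes. The smallest permitted pool, two sites, gives 2 × 100 = 200, below the milk-centile target of 244 to 255. That target was set for milk nutrients, so this is a matter of consistent labelling and has no bearing on site-specific values.

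**What to change.** 1. State whether 250 per site is the number recruited or the number evaluable at each visit, and make the Abstract, Study design and settings, and the sample-size sections agree.
2. Under Estimating centiles, replace the bare 255 with a short table of per-site precision at the evaluable number per visit, for example 250, 225 and 200, and state the multiplier used.
3. Qualify the Discussion sentence: single-site reference values will be reported with their confidence intervals and achieved precision. The caveat written for the 100-sample analytes, that within-site percentiles are not reference values, need not be extended to them.
4. Separately, under Sample size estimates for other analyses, tie the reference-value label to about 250 pooled samples, reached with a third site (3 × 100 = 300) or the banked samples already mentioned.

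Items 1 to 3 cost wording and one small table, with no new data collection. Item 4 may mean extra assays on banked samples, or loss of the reference-value label for some secondary analytes when only two sites pool.

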#### Blood

A venous blood sample is collected into an EDTA vacutainer from the mother on visits 2, 3, and 4. Fasting overnight or for 3–4 h prior to blood collection was ideal if possible. The mother's recall of the time of her last meal is recorded. A venous sample is collected from all infants at visit 2, and to reduce the number of infant blood draws to a total of 2, from 50% of infants at visit 3 and the other 50% at visit 4, randomly selected. In The Gambia, however, 100% of infants are sampled at each visit as well as the mother during pregnancy. The mother's recall of the time of the infant's last meal is also recorded.

Plasma is obtained by centrifugation of the blood sample at 1500 × *g* for 10 min at 4°C. The plasma is stored in aliquots in amber tubes. The buffy coat is collected into a DNAse/RNAse-free, sterile tube. The volume of the remaining RBCs is determined in order to wash the RBCs with an equal volume of 0.9% saline solution. The RBCs are centrifuged again and the supernatant is removed. This procedure is repeated until the supernatant is clear. After diluting with equal amounts of deionized water, the washed RBCs are aliquoted into amber tubes for storage. All aliquots are then frozen and stored at 70°C until analysis.

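### Pooling two sites does not by itself secure the plan's own precision standard for infant blood reference values: it falls short for 100-sample analytes, and for pairs without The Gambia at visits 3 and 4 once a few samples are lost

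*Protocol article*

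**What the plan says.** Under Estimating centiles, the article derives its precision standard: "This requires an overall sample size of 255 per time point". The stated aims are "to avoid overlap between the 95% CIs around the 5th and 10th centiles" and "to estimate the sample median within 5 centiles with 95% confidence".

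The same section then turns to blood. It accepts that samples will probably be missing for some participants and that numbers will be lower. It concludes that, if it is found "acceptable to pool information from ≥2 study sites to construct RVs for infant blood variables, the precision of the estimate will be acceptable". No count and no tolerable loss are attached.

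Two other sections fix how many infant samples there can be:

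- **Blood.** All infants are bled at visit 2. After that, samples are taken "from 50% of infants at visit 3 and the other 50% at visit 4, randomly selected". The Gambia is the exception and samples every infant at each visit.
- **Sample size estimates for other analyses.** For some secondary outcomes, with infant plasma free amino acids as the example, "only 100 samples for each site and time point are analyzed". The working assumption is that values are "similar enough to pool between ≥2 of the sites". Only if pooling proves impossible are the percentiles presented with a warning that they are not reference values (RVs). Banked samples may be used if more than 100 turn out to be needed.

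**The concern.** The pooling condition counts sites, while the precision standard counts observations. The two agree only if any two sites supply enough infant samples. Half-sampling at visits 3 and 4 and the limit of 100 per site both reduce that supply, so the assurance may not hold at its own minimum of two sites.

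What is at stake is labelling. Table 6 lists blood micronutrient status of mothers and infants among the secondary outcomes used to construct RVs. Under the present wording, centiles from a two-site pool could be issued as RVs without the caveat even where the pooled number misses the plan's own definition of adequate. Two-site pooling is a realistic outcome: the Data analysis plan allows RVs from only two or three pooled sites, and the Discussion says site differences may prevent combining data.

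**Working it through.** **Inputs.** Formula (2) under Estimating centiles: SE = (σ/√n) × √(1 + 0.5z²). Planned dyads: 250 per site and time period. Infant blood at visits 3 and 4: 125 per site in Bangladesh, Brazil and Denmark, and 250 in The Gambia. Restricted analytes: 100 per site and time point. Loss rate: not given, so 5% and 10% below are assumptions.

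**Step 1: the plan's 255.** The factors √(1 + 0.5z²) are 1.534 for the 5th centile (z = −1.645) and 1.350 for the 10th (z = −1.282). The gap between these centiles is 1.645 − 1.282 = 0.363 SD. With multiplier c:

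- No overlap: n = [c × (1.534 + 1.350) / 0.363]²
- Median within 5 centiles: n = [c / 0.1257]², where 0.1257 is the normal deviate of the 55th centile

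With c = 1.96 these give 242 and 244. With c = 2 they give 252 and 254. With c = 2.01 (t on 49 df) they give 255 and 256. So 255 is reproduced with a multiplier of about 2, and strict 1.96 gives 244.

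**Step 2: pooled numbers against both criteria (c = 1.96).** The sum of half-widths is 1.96 × (1.534 + 1.350)/√n and must stay below 0.363.

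| Pool | n | Sum of half-widths (SD) | Median, ± centiles | Both met |
|---|---|---|---|---|
| Two sites of 100 | 200 | 0.400 | 5.51 | No |
| Two sites without The Gambia, visit 3 or 4, 10% loss (assumed) | 225 | 0.377 | 5.20 | No |
| Same, 5% loss (assumed) | 238 | 0.366 | 5.05 | No |
| Same, no loss | 250 | 0.357 | 4.93 | Yes |
| Plan's requirement | 255 | 0.354 | 4.88 | Yes |
| Three sites of 100 | 300 | 0.326 | 4.50 | Yes |
| The Gambia plus one site, or the three other sites, visit 3 or 4 | 375 | 0.292 | 4.03 | Yes |
| Any two sites, visit 2, full analysis | 500 | 0.253 | 3.49 | Yes |

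**Step 3: tolerable loss.**

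- From 250, the median criterion (244) fails once losses exceed 6/250 = 2.4%. The overlap criterion (242) fails once they exceed 8/250 = 3.2%.
- From 375, the pool stays at or above 255 until losses exceed 1 − 255/375 = 32%.
- From 300, the corresponding limit is 1 − 255/300 = 15%.

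**Step 4: what banked samples can add.** At visit 2 each site plans 250 infant samples, so a two-site pool can be raised well above 255. At visits 3 and 4, a pair without The Gambia cannot exceed 250 even if every sample is analysed.

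**The case against.** Several counter-arguments have force.

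- **The standard was set for milk.** The sample size basis names breast milk nutrients, and blood is secondary. The blood statement calls precision acceptable without saying that 255 is met. This is fair: applying the standard to blood is an inference. But the statement follows directly on the 255 derivation, and the article offers no other measure of acceptable.
- **250 is adequate.** It meets both criteria at 1.96 and is only 2% below 255, and the Discussion treats the numbers per site as enough for site-specific RVs. This stands, so case (b) depends wholly on lost samples. The article itself expects missing blood, and Table 3 and the Data analysis plan remove further dyads, but no rate is stated.
- **Banked samples are available.** True, and this softens case (a). No count triggers their use, however, and they cannot lift a visit 3 or 4 pair without The Gambia above 250.
- **The loss of precision is modest.** At 200 the standard error is about 13% larger than at 255. Formula (2) is a generic sizing device, and the final centiles will come from regression models and smoothing. This limits the consequence but does not reconcile the statement with the stated criteria.

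A reader might infer that infant blood RVs fail generally at visits 3 and 4, or that every 100-sample analyte fails. The figures do not support either: three of the six possible pairs include The Gambia and plan 375, and three sites of 100 give 300. Nor does interval overlap mean that the 5th and 10th centiles cannot be told apart. Under formula (1) both come from one mean and SD and are always ordered. Overlap means only that the plan's own target is missed.

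**Conclusion.** The assurance is not secured at its two-site minimum in two cases.

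(a) Two pooled sites of 100 give n = 200, which is 22% below 255. Both criteria fail with no losses at all unless banked samples are added.

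(b) At visits 3 and 4, two sites without The Gambia plan 250 at most. Both criteria are just met with complete sampling, and both fail once losses pass about 3%.

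The conclusion assumes that acceptable precision means the criteria stated in the same section, and that formula (2) with 1.96 is the yardstick. With a multiplier of 2, even a complete 250 falls marginally short of 252 and 254. Case (b) also assumes some loss, which the article calls likely but does not quantify. Milk RVs are not touched by this point. It concerns which secondary blood percentiles are labelled as RVs, and it is worth correcting because the fix is cheap.

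**What to change.** In Estimating centiles (the blood paragraph) and in Sample size estimates for other analyses, replace the condition of two or more sites with a minimum pooled number actually analysed at that time point. Set it equal to the plan's own requirement. The authors should fix one figure: 255 as stated, or 244 if 1.96 is meant. The choice matters, because a complete pool of 250 passes under the second and not the first.

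Where the number is not reached, analyse banked samples if they exist. Otherwise attach the existing caveat that the percentiles should not be treated as RVs, and extend it to pooled as well as within-site results.

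The cost is about one sentence in each section, plus possible extra assays. The downside is that some two-site blood percentiles would carry the caveat.
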